## Abstract

**Background:**

In between episodes of (hypo) mania and major depression, people with bipolar disorder can experience ongoing low mood or mood instability, and these may also be present as part of cyclothymic disorder. This is a phase II evaluation of an adapted form of behavioural therapy (STABILISE) for inter-episode bipolar symptoms. The study aims to establish the feasibility and acceptability of the therapy and research procedures, including an economic component, to inform a future definitive trial.

**Methods:**

Patients will be randomised 1:1 to either Treatment as Usual (control arm) or Treatment as Usual plus STABILISE intervention (intervention arm). Follow up points will be at 14, 30 and 52 weeks post eligibility confirmation, with 30 weeks as the primary end point. We aim to recruit 60 individuals meeting diagnostic criteria for a Bipolar Spectrum Disorder, and reporting ongoing bipolar symptoms (low mood or mood instability) outside of a manic or severe depressive episode. Feasibility and acceptability will be examined through recruitment and retention rates, completion rates for the candidate primary outcome measures (PHQ9, ALS-SF, QoL.BD and BRQ) and feedback from participants on their experience of study participation and therapy. Proceeding to a definitive trial will be indicated if the following criteria are met: (i) trial participation is deemed, or can be made, sufficiently safe; (ii) recruitment rate indicates that larger-scale recruitment would be feasible (recruitment rate of at least two participants per month within at least one site, with mitigation plan if overall target sample size not met); (iii) for candidate primary outcome measure follow up data is available at 30 weeks from at least 75% of participants, or from between 55 and 74% with clear plan for improvement.

**Discussion:**

This study is a randomised, controlled feasibility trial that builds on an initial case series of the STABILISE approach. The findings will be used to establish whether a future, definitive trial is feasible and to refine the research procedures and therapy protocol.

**Trial registration:**

ISRCTN18207465. Registered 13th March 2024, https://www.isrctn.com/ISRCTN18207465.

**Supplementary Information:**

The online version contains supplementary material available at 10.1186/s40814-025-01678-6.

## Background

Bipolar spectrum disorders (Bipolar I or II Disorder, Cyclothymic Disorder) result in substantial personal and societal costs and affect around 1 in 20 people across their lifetime [1, 2].

In addition to major episodes of depression or mania, people with bipolar spectrum disorders can experience ongoing bipolar symptoms (inter-episode Bipolar symptoms (IEBS)). With IEBS, depressive symptoms tend to be more frequent relative to hypomanic symptoms [3] and instability of mood is common [4].

Interventions are needed for IEBS for three reasons. First, they are common: ongoing bipolar symptoms in the form of subclinical low mood or mood instability are experienced by up to half of those with Bipolar I or II Disorder who are not in a major episode [5], and on average people with bipolar I or II disorder spend around twice as long experiencing residual symptoms as they spend in acute episodes [3]. Second, they are associated with significant distress and impairment, including increased psychiatric comorbidity and poorer functioning [4–9]. Third, the ongoing mood instability that constitutes cyclothymic disorder is associated with risk of developing full depression and mania [10], which can be costly to the health service and the wider society, and costly to patients and families [2].

Despite the impact of IEBS, studies evaluating approaches to helping people with this disabling presentation are scarce. Furthermore, whilst some have examined the effects of pharmacological agents on residual symptoms [11], relatively few consider their impact on mood instability.

Psychological therapies for individuals with bipolar disorder are valued by service users, and are recommended within various national treatment guidelines, yet the extant literature does not provide direct guidance on the optimal psychological treatment for people with IEBS, with studies tending to focus on relapse prevention or alleviation of acute depression as the primary target of therapy [12] or specifically upon cyclothymic disorder [13]. Thus, we do not currently have a psychological treatment that seeks to address the common ongoing mood symptoms (subclinical low mood and mood instability) that people with bipolar disorder (BD) or cyclothymic disorder (CD) present with, nor a therapy that has been tested across the bipolar spectrum with respect to these issues.

Our approach (STABILISE: Study of Therapy for Bipolar Interepisode Symptoms) brings together two behavioural therapies that are commonly used and effective with related populations to address key therapy targets also relevant to IEBS: reduction of depressive symptoms through supporting meaningful behaviours, and management of problematic affective instability. The resulting therapy is designed to support people with BP or CD in managing ongoing difficulties with low mood or mood instability, including the impact of these on everyday life.

Behavioural activation (BA) is used extensively in the treatment of acute unipolar depression [14, 15]. It is informed by the behavioural theory of depression whereby depression is hypothesised to be maintained by a reduction in access to positive reinforcement from the person’s context, and a subsequent increase in ‘avoidance’ behaviours that function to reduce negative affect rather than to approach valued goals. Correspondingly, BA involves supporting the person to access previous and new sources of reward through scheduling goal and value-consistent activities into the week and learning or re-accessing skills for managing barriers to engaging fully in these activities. BA is often considered to represent a parsimonious and relatively straightforward approach to disseminate, potentially reducing training costs and broadening the range of health professionals who may be able to deliver it [16]. Two reports of case series data on its use in people with acute bipolar depression [17, 18] describe high acceptability rates, no safety concerns and encouraging patterns of change on clinical outcome measures.

Dialectical behaviour therapy (DBT) is a form of behavioural therapy originally developed for women with borderline or emotionally unstable personality disorder [19, 20] and later applied across genders and across multiple problem areas. It is based upon the biosocial theory which posits that emotion dysregulation is the outcome of an interaction between an emotionally sensitive temperament and an early environment that invalidates their emotional responses. DBT teaches the person skills for recognising and responding to emotional states, and for managing the situations that can trigger these responses. A behavioural framework is used to understand the interaction between the person and their context, and the therapist stance models appropriate validation of emotion and a dialectical outlook, whereby it is acknowledged that two seemingly contradictory accounts can both be true (e.g. ‘I am an okay person and I can adapt my behaviours in this context to get a better outcome for myself and others’.

The full DBT programme includes group skills training, individual therapy sessions, skills coaching outside of sessions, structuring the environment and group consultation between therapists; however, partial versions of DBT, often called DBT-informed interventions, have been developed. DBT, including DBT-informed interventions, has been tested for a range of patient groups, including people without a diagnosis of personality disorder, where emotional dysregulation plays a role in the presenting issues [21–23]. It has found to be effective in reducing substance use and self-harm (both being behaviours that are often used by individuals to cope with intense, seemingly unmanageable affect) and problematic anger. A small number of case series and feasibility studies have explored DBT-informed interventions for people with bipolar disorder, with promising outcomes in terms of acceptability and likely clinical benefit; these vary in the extent to which they adhere to the traditional DBT programme versus include concepts and techniques influenced by DBT or other emotion regulation programmes [24]. In addition, except for one study [25], these studies do not focus specifically on inter-episode symptoms or include individuals with cyclothymic disorder.

With input from people with lived experience of bipolar disorder, and family members, we integrated concepts and techniques from DBT within a BA protocol used previously with individuals with bipolar depression [18]. An initial examination of the safety and acceptability of the resulting therapy was conducted within in a case series of 12 individuals with BD or CD and ongoing low mood or mood instability. At the time of writing, the acute treatment phase of the case series is complete and pre-determined rules to allow progression to the next phase of evaluation, a randomised controlled feasibility trial, have been met (no serious concerns about therapy safety; instances of reliable improvement exceed instances of reliable deterioration). The protocol for this feasibility trial is presented here.

The overall aim of this study is to determine the likely feasibility, acceptability and safety of the research procedures, including the therapy protocol, to design a future definitive randomised trial to determine the clinical and cost effectiveness of the STABILISE therapy programme.

## Objectives

(i)To inform the recruitment and timeline of a future fully-powered trial, by informing estimates of the number of participants who will need to be identified, approached, consented, randomised and who are likely to complete outcome assessments.(ii)To refine future trial procedures by establishing the acceptability and experience of the trial process to participants. This includes acceptability and experience of randomisation and outcome measures.(iii)To inform selection of the optimal primary outcome measure in a future trial by assessing the performance of selected candidate primary outcome measures with respect to level of acceptability to participants and participant-perceived relevance and value. Although not powered to detect a significant between group mean difference, we will scrutinise between group mean differences for each outcome measure, as well as relative rates of reliable improvement and deterioration, to assess sensitivity of the measure to the impact of the intervention.(iv)To inform estimation of sample size for a future trial by measuring data completeness at follow up (participant attrition) and standard deviation of the likely primary outcome measure (to compare to reports in published literature).(v)To characterise the comparator condition, treatment as usual, across individuals and sites.(vi)To further explore the safety and acceptability of the treatment and, based on input from trial participants and clinicians, to further refine and develop the treatment manual and the procedures for training, supervising and assessing the competence of trial therapists.(vii)To demonstrate feasibility outside of the lead site by including a second site.(viii)To estimate the cost of the intervention.(ix)To assess the feasibility of collecting health care resource utilisation data and health-related quality of life data using the EQ-5D-5L [26].(x)To explore the feasibility of collecting momentary assessment (experience sampling) data at three time points (5 times per day, for 10 days, at each timepoint): the ultimate purpose of collecting these data in a future larger trial is to estimate mood instability and to examine process of change.

The criteria for progression to definitive trial are given in Table 1, presented in accordance with the framework proposed by Avery and colleagues [27].

**Table 1 Tab1:** Criteria for progression to a definitive trial

	Red		Amber		Green	
Overall safety of intervention and trial procedures as determined by TSC and sponsor^a^	Cannot be made sufficiently safe for use in a definitive trial		Can be made sufficiently safe following modification		Sufficiently safe for use in a definitive trial	
Mean recruitment rate per site over 15 months	< 2 participants per month at both sites		< 2 participants per month at one site and target sample size not reached, with clear plan for improvement		≥ 2 participants at both sites OR < 2 participants at one site but overall target sample size reached^b^	
Outcome measure completion at 30-week follow-up point (completion of candidate primary outcome measure at primary end point)	< 55% of participants		Between ≥ 55 and < 75% of participants, with clear plan for improvement		≥ 75% of participants	
Level of completion of intervention (defined as attending at least 6 therapy sessions)^c^	< 50% of participants		50–89% of participants, with clear plan for improvement		≥ 90% of participants	

Red: Do not progress to the main trial (unless TSC agree exceptional circumstances and a mitigation plan is present); Amber: Progress if action plan to mitigate problems can be determined and agreed with the Trial Steering Committee (TSC); Green: Progress directly to the main trial

^a^Subsequent to reviewing information on adverse and serious adverse events arising during the trial

^b^To allow for a situation in which recruitment systems require a lead-in period at a site before becoming optimized, and this optimization period can then be accounted for in planning for a definitive trial

^c^Information will be collected on reasons for discontinuation to inform plan for enhancing retention in intervention and/or refinement of the estimand for a definitive trial [28]

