### Design

This feasibility study has a two-arm randomised parallel controlled trial design. Participants will be randomised on a 1:1 ratio to Treatment as Usual (TAU) only (control arm) or TAU plus STABILISE programme (intervention arm). Outcome measures will be completed at baseline and at three follow-up points: 14, 30 and 52 weeks post study entry. We have selected 30 weeks as the primary end point to allow this to be immediately following the intervention period. The study takes a mixed-method approach whereby evaluation of therapy acceptability and potential impact is explored both qualitatively and quantitatively.

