### Sample size

A total of 60 individuals will be recruited (target *n* = 30 in Devon, and *n* = 30 in Avon & Wiltshire). A sample size of 60 participants allows estimation of loss to follow-up within ± 12 percentage points, assuming 20% attrition, and is sufficient to estimate the standard deviation in the candidate primary outcome measures [35, 36].

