#### Patient-reported clinical outcome measures

In addition to the PHQ-9 and ALS, the following clinical outcome measures will be completed at baseline, 14, 30 and 52 week follow-up (see Additional File 2 for measure details): Bech Rafaelsen Mania Scale (BRMS [40], Brief Quality of life in Bipolar Disorder scale (QoLBD [41], Generalised Anxiety Disorder Questionnaire (GAD-7 [42]), Bipolar Recovery Questionnaire (BRQ [43]), Life chart self-report (a self-report of number and duration of depressive and manic episodes in the period since last assessment, completed at 14, 30 and 52 week follow-up points only, with the support of the researcher; Health Economics Questionnaire (HEQ [44]), EQ-5D-5L (health related quality of life). At this stage, candidate future primary outcome measures include the PHQ-9, ALS, QoL.BD and BRQ.

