## Data analysis

### Statistical analyses

Given the feasibility design, data analysis will focus on a descriptive analysis of the feasibility objectives of the study. We will report recruitment rates (average number of participants recruited per month) overall and by site. Retention and completion of outcome measures at follow-up timepoints will be reported as numbers and percentages, overall and by each treatment group. Participant characteristics at baseline will be reported descriptively for each treatment group, using mean (SD) for continuous variables, and percentages for categorical variables.

Outcome measures will be reported descriptively for each treatment group at baseline and at each post-randomisation follow-up, i.e. 14, 30 and 52 weeks. For 30- and 52-week follow-up data, the between group mean differences for continuous variables (intervention minus control group) will be reported with a 95% CI. The between group mean difference will be derived from a linear regression model, which will include treatment group as a fixed effect and will also adjust for study site and use of medication for BDs (factors used in the randomisation procedure). The feedback questionnaire will be reported descriptively for those items that relate to the STABILISE + TAU group only; the overall satisfaction item will be reported descriptively by treatment group and with a between group mean difference and 95% CI (using a linear regression model as for the clinical outcomes).

Given the feasibility nature of the trial, all participants will be analysed according to their randomised group irrespective of treatment actually received (intention to treat principle). Analyses will include observed data only; no imputation of missing outcome data will be performed. To explore potential mechanisms of missingness, we will report the mean (SD) for baseline PHQ-9 and GAD-7 for participants with and without completion of all four potential primary clinical outcome measures at 14 weeks, overall and by treatment group.

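### The between-group differences meant to show how sensitive each candidate outcome is are in each scale's own units and not adjusted for baseline score, so they cannot be compared across measures and are less precise than they could be

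*Protocol article*

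**What the plan says.** Objective (iii) is to inform the choice of primary outcome for a later trial. It names acceptability and participant-perceived relevance and value first. It then concedes that the trial is not powered for group differences and adds that "we will scrutinise between group mean differences for each outcome measure, as well as relative rates of reliable improvement and deterioration, to assess sensitivity" of each measure to the intervention. Under Patient-reported clinical outcome measures, "candidate future primary outcome measures include the PHQ-9, ALS, QoL.BD and BRQ". These are completed at baseline and at 14, 30 and 52 weeks.

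Statistical analyses fixes the statistic: at 30 and 52 weeks "the between group mean differences for continuous variables (intervention minus control group) will be reported with a 95% CI". The difference comes from a linear regression on treatment group, study site and use of medication. No standardisation is stated, and the outcome's baseline score is not among the listed covariates. On missing data: "Analyses will include observed data only; no imputation of missing outcome data will be performed".

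Sample size says "A total of 60 individuals will be recruited" and justifies this by loss to follow-up and by estimation of SDs, not by comparison of measures.

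**The concern.** Sensitivity helps to choose between four instruments only if the four can be compared. A difference in PHQ-9 points and a difference in ALS points have no common unit. The entry cut-offs in Setting and participants (5 on PHQ-9, 1.3 on an ALS subscale) show how far apart the scales lie. The stated statistic therefore does not answer the stated question for this half of the evidence.

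The model also omits the baseline score, usually the strongest available predictor of a symptom or quality-of-life score at follow-up. Every interval is then wider than it needs to be, in a trial where precision is already short. At stake is the quality of the evidence for a named objective, which feeds the choice of primary outcome for the definitive trial.

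**Working it through.** **Inputs.** Planned n = 60, 1:1 allocation and 20% attrition (Design; Sample size). Observed data only (Statistical analyses). Four candidate measures. The documents give no SDs, no correlations and no expected effects, so the work is in SD units and the correlations are assumptions shown as ranges.

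**The plan's own figure.** The article says "A sample size of 60 participants allows estimation of loss to follow-up within ± 12 percentage points, assuming 20% attrition". For 12 of 60:
- Wald: 1.96 × √(0.2 × 0.8/60) = ±10.1 points.
- Wilson: 11.8% to 31.8%, so −8.2/+11.8 points.
- Exact: 10.8% to 32.3%, so −9.2/+12.3 points.

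The stated 12 matches the longer side of the Wilson or exact interval after rounding. It is sound, but it concerns attrition and not the comparison of measures.

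**Observed sample.** 60 × (1 − 0.20) = 48, about 24 per arm.

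**One measure, standardised.** SE = √(1/24 + 1/24) = 0.289 SD. The 95% half-width is 1.96 × 0.289 = 0.57 SD (0.58 with a t quantile).

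**Gap between two measures in the same participants.** SE = 0.289 × √(2(1 − ρ)), where ρ is the correlation between the measures. The 95% half-width is:

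| ρ (assumed) | Half-width (SD) |
|---|---|
| 0.3 | 0.67 |
| 0.5 | 0.57 |
| 0.7 | 0.44 |

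Plausible gaps of 0.1 to 0.2 SD between measures lie well inside these limits. The per-measure intervals that are planned do not show this quantity.

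**Cost of omitting the baseline score.** With baseline–follow-up correlation r, adjustment multiplies the SE by √(1 − r²).
- r = 0.4: √0.84 = 0.917. The adjusted half-width is 0.57 × 0.917 = 0.52 SD, and the unadjusted interval is 1/0.917 = 1.09 times as wide.
- r = 0.7: √0.51 = 0.714. The adjusted half-width is 0.57 × 0.714 = 0.40 SD (0.404 unrounded), and the unadjusted interval is 1/0.714 = 1.40 times as wide.

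So the planned interval is about 9% to 40% wider than the adjusted one. Put the other way, adjustment shortens it by about 8% to 29%.

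**Reliable-change rates.** These are proportions, so units are no obstacle, but they are no more precise. For an assumed 40% against 20%, the half-width is 1.96 × √(0.4 × 0.6/24 + 0.2 × 0.8/24) = 0.25, or 25 points.

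**How informative the observed order would be.** With true standardised effects of 0.4/0.3/0.3/0.3 (assumed), the best measure shows the largest observed difference 37%, 39% and 43% of the time for ρ = 0.3, 0.5 and 0.7. With 0.5/0.3/0.3/0.3 the figures are 50%, 55% and 63%. Chance is 25%. The order is weak evidence, but it is better than chance when true gaps exist.

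**The case against.** The strongest reply is that the article states no procedure that could go badly wrong. Objective (iii) puts acceptability and perceived relevance first, and Additional measures adds participants' own ranking of the measures. The lack of power is admitted in the same sentence, reliable-change rates are free of scale units, and each difference carries a 95% CI. Reported SDs would let a reader standardise by hand. Outcomes and measures also refers to Additional File 3 for how each objective is assessed, and that file or an analysis plan may already cover standardisation.

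Much of this stands. A reader might infer three stronger things that the documents do not support:
- **That the plan ranks the measures by observed effect and picks the largest.** No such rule is stated; the only rankings described are the participants'.
- **That an inflated effect will be used to size the definitive trial.** Objective (iv) takes attrition and the SD from this trial, and no effect.
- **That the comparison is little better than chance.** The figures above say otherwise, and they rest on assumed effects and correlations.

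The reply does not remove the core. The article does not leave the model open: it names the statistic and the covariates, and objective (iii) puts that statistic to a use for which its units are unsuited. The admission about power concerns differences between groups, whereas this use compares measures. Standardising by hand would cure the units but not the missing baseline adjustment.

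**Conclusion.** The point holds as an improvable choice of metric and model, not as a flaw in how the outcome will be chosen. As written, the mean differences meant to inform sensitivity cannot be compared across the four candidates, and their intervals are about 9% to 40% wider than baseline-adjusted ones (assuming r of 0.4 to 0.7). Even on a common scale the evidence stays imprecise: about ±0.57 SD for one measure and ±0.44 to ±0.67 SD between two, before baseline adjustment. These figures assume 48 observed, equal arms and inter-measure correlations of 0.7 to 0.3. Sensitivity evidence of this precision can support the choice of outcome but should not lead it.

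**What to change.** 1. In Statistical analyses, add the baseline score of each outcome to the regression wherever it was collected. The satisfaction item and the life chart have no baseline and stay as they are.
2. For the four candidates, also report the adjusted difference divided by a stated SD (for example the pooled baseline SD), with its 95% CI, next to the reliable-change rates.
3. In objective (iii), state that the sensitivity evidence is descriptive and secondary to acceptability, completion and participant ranking, and give the expected precision as the reason.
4. Optionally, give participant-level bootstrap intervals for pairwise contrasts between measures. No significance threshold should be attached to them.

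The cost is a few sentences and slightly more analysis; no new data are needed. The choice of SD must be stated because it is not neutral: entry requires either PHQ-9 of at least 5 or the ALS subscale at 1.3 or more, which may narrow the baseline spread of those two measures and make their standardised differences look larger. If Additional File 3 or an analysis plan already specifies any of this, the article's model description should be brought into line with it.

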## Trial Status

The start date of the trial was 28th March 2024. Recruitment is running from April 2024 to June 2025 inclusive. Follow up will last 52 weeks, with the entire study period lasting for 28 months.

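### Table 1's recruitment rule: Red ignores the total, so 29 + 29 is Red while 30 + 0 is Amber; and Green sets no minimum for the weaker site

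*Protocol article*

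**What the plan says.** The recruitment row of Table 1 (protocol article, Objectives) is headed "Mean recruitment rate per site over 15 months". Its three cells are:

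- **Red:** fewer than 2 "participants per month at both sites". The total is not mentioned.
- **Amber:** fewer than 2 "participants per month at one site and target sample size not reached, with clear plan for improvement".
- **Green:** at least 2 at both sites, or fewer than 2 "participants at one site but overall target sample size reached". This cell does not repeat the words for a monthly rate, but the row heading leaves no other sensible reading.

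Footnote b explains Green's second limb as an allowance for a lead-in period at a site. The notes under the table say that Red means no progression unless the TSC agrees exceptional circumstances with a mitigation plan, that Amber needs an action plan agreed with the TSC, and that Green means direct progression.

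The Abstract (Methods) uses the same boundary: "recruitment rate of at least two participants per month within at least one site", with a mitigation plan if the overall target is missed. The Sample size section sets the target at 60, 30 per site. Objective (vii) is "To demonstrate feasibility outside of the lead site by including a second site".

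**The concern.** A traffic-light rule should place a near miss in the middle band and a serious shortfall in the bottom band. This row can do the opposite. Two sites that each fall one participant short get the worst colour, while one site on target beside a site that recruits nobody gets the middle one. At the top of the scale, the wording names both sites but never tests the weaker one, although a second site was included in order to test feasibility away from the lead site.

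At stake is a central output of this feasibility trial: whether the definitive trial goes ahead, and on what terms. In a plausible near-miss the TSC would have to invoke an override meant for exceptional circumstances in order to reach what should be a routine Amber decision.

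**Working it through.** **Inputs.** Window of 15 months (Table 1). Trial Status agrees: "Recruitment is running from April 2024 to June 2025 inclusive" is 9 months in 2024 plus 6 in 2025. Rate threshold of 2 per month per site (Table 1). Target of 60, 30 per site (Sample size).

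**Reproducing the target.** 2 per month × 15 months = 30 per site, and 30 × 2 sites = 60. The threshold rate is exactly the rate that delivers the full target, so a site is below 2 per month whenever it has 29 or fewer (29/15 = 1.93).

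**Classifying pairs of site counts by the literal wording.**

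| Site counts | Total | Monthly rates | Colour |
|---|---|---|---|
| 29 + 29 | 58 (97% of target) | 1.93, 1.93 | Red |
| 28 + 30 | 58 | 1.87, 2.00 | Amber |
| 30 + 0 | 30 (50% of target) | 2.00, 0 | Amber |
| 29 + 30 | 59 | 1.93, 2.00 | Amber |
| 29 + 31 | 60 | 1.93, 2.07 | Green |
| 60 + 0 | 60 | 4.00, 0 | Green |

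Over all pairs, Red covers totals 0 to 58, Amber 30 to 59, and Green 60 or more. For every total from 30 to 58, the split alone decides between Red and Amber.

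**Equal recruitment.** For n + n, n ≤ 29 is Red and n ≥ 30 is Green, so Amber cannot occur. The plan's own 30/30 split is thus the case with no middle band. The other numeric rows of Table 1 have wide ones (55% to below 75%; 50–89%).

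**What Green tests.** If both sites have at least 30, the total is at least 60. If the total is at least 60, at least one site has 30 or more, because 29 + 29 is only 58; one of Green's two limbs is then met. Green is therefore equivalent to a total of at least 60, and the per-site wording adds nothing.

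**How often.** Assume independent Poisson counts with no cap on recruitment; the documents state no model. With site means 15r₁ and 15r₂, P(Red) = P(X₁ ≤ 29) × P(X₂ ≤ 29), P(Green) = P(X₁ + X₂ ≥ 60), and Amber is the remainder.

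| True rates per month | Expected total | Red | Amber | Green |
|---|---|---|---|---|
| 2.0 and 2.0 | 60 | 0.476² = 0.23 | 0.26 | 0.52 |
| 1.8 and 1.8 | 54 | 0.693² = 0.48 | 0.30 | 0.22 |
| 2.2 and 0.5 | 40 | 0.28 | 0.72 | <0.01 |
| 3.5 and 0.5 | 60 | <0.01 | 0.48 | 0.52 |

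The pair expecting 54 meets Red more often than the pair expecting 40. The first and last rows have the same chance of Green, although in the last row the weaker site expects only 7.5 participants.

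**The case against.** The row is about rate per site, not about the total. One site that shows 2 per month is achievable is different evidence from no site showing it, and the Abstract draws the same line, so the documents agree with each other. Adding a participant at either site never worsens the colour. All of this stands. It does not explain why 58 of 60 should fall below 30 of 60, or why equal recruitment should have no middle band.

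Three stronger readings are tempting and are not supported:

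- **That the rule is disordered from Red through to Green.** It is not. Green always needs at least 60, so 60 + 0 Green against 29 + 29 Red is in the right order by total. The fault at 60 + 0 is only the untested second site. It is also an extreme case, needing one site to double its target, although no cap or site minimum is stated.
- **That a near-complete trial would be stopped.** Red does not stop this trial. It governs progression to a later one and carries a TSC override.
- **That a lead-in at both sites necessarily gives Red.** Faster later months could bring a 15-month mean back to 2.

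It is also fair to say that a weak second site would be visible, since Statistical analyses promises recruitment rates overall and by site. But the written rule would still say to progress directly.

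**Conclusion.** The concern holds in two separate parts. First, Red and Amber are out of order when judged by total recruitment (58 can be Red, 30 can be Amber), and there is no Amber band when the sites recruit equally. Second, Green amounts to a total of at least 60 and can be met without evidence from the second site. Both parts follow from the wording and arithmetic alone. The probabilities (Red about 23% at a true 2.0 per month at each site, about 48% at 1.8) depend on the Poisson assumption and are only illustrative.

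Severity is moderate. No estimate, randomisation or safety procedure is affected, and the override limits the harm, but a stated decision threshold gives a poor answer close to the planned scenario.

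**What to change.** 1. **Red/Amber boundary.** Use one total-recruitment floor, set by the TSC, whatever the split between sites: Red only if the total is below the floor, Amber if it is at or above the floor but below 60. A floor of 30, the smallest total that Table 1 already accepts as Amber, restores the order without turning any present Amber case Red. A higher floor also works, provided it applies equally to cases such as 30 + 0. Adding a floor only to the existing both-sites condition would not do: with a floor of 45, 22 + 22 = 44 would stay Red while 30 + 0 = 30 stayed Amber.
2. **Green's second limb.** Add a TSC-set minimum for the weaker site; if it is not met, the result is Amber. The split then matters between Amber and Green by design, because objective (vii) concerns the second site.
3. **Abstract.** Align the recruitment clause with the revised row.

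**Cost.** One table row and one clause are reworded. Red becomes harder to reach with a low floor: at 30, a split of 15 + 15 would move from Red to Amber. Green becomes harder to reach on one site's recruitment. The main downside is that a pre-specified rule is amended during or after accrual. The change should therefore be dated, agreed with the TSC (ideally before final site counts are reviewed), and the colour reported under both the published and the revised wording.
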